### Intervention Description

The Brain CareNotes mobile telehealth app (Figure 2; [44]) is used by care partners for BPSD management. It includes remote communication with an external human support person—a care coach—as well as features for users to independently perform health-related activities (Textbox 1 [45,46]).

**Figure 2 figure2:**
[figure not shown]
Brain CareNotes features.

Brain CareNotes mobile telehealth app features.Care skill support features: users have 24/7 access to written and visual materials on developing care skills. These materials cover a range of topics, including (1) care partner burden, (2) understanding the patient with memory loss, (3) exercise, (4) personal care, (5) behaviors, (6) safety, and (7) delirium.Care coach support: each care partner user is assigned to a personal care coach employed by the study team. Care coaches operate remotely using a mobile phone or computer-based secure and HIPAA (Health Insurance Portability and Accountability Act)–compliant portal. Care coaches perform the following tasks daily: (1) monitor, respond to, and initiate messages to and from Brain CareNotes users; (2) address user activity, including new assessments; and (3) schedule and conduct biweekly or monthly phone calls with the care partner.Assessments and tracking: every 2 weeks, users are prompted to self-administer the Healthy Aging Brain Care Monitor [45,46]. Once an assessment is completed, results are immediately displayed in easy-to-read, color-coded visualizations with interpretation of whether scores are normal, mild, moderate, or severe. Past measurements can be displayed on demand to compare recent scores and assess change over time. Care coaches receive daily notifications when an assessment was completed or a message was received from a care partner.Responding to change over time: Brain CareNotes has bidirectional secure messaging, allowing unpaid care partner users to communicate back and forth with the care coach or for the care coach to initiate a conversation. Moreover, when a care partner reports a patient or care partner symptom, the app generates a set of specific CareNotes associated with each reported symptom.

Participants randomized to receive Brain CareNotes will be sent a HIPAA (Health Insurance Portability and Accountability Act)–compliant link to create an app account on their personal device. This researcher-generated link is required to gain access to Brain CareNotes. If the participant does not have a mobile device meeting the minimum technical requirements, a smartphone with an unlimited network data plan from AT&T, along with unlimited text messaging and pooled voice minutes, will be provided for the duration of the study.

An unmasked research assistant will guide the participant through loading the Brain CareNotes app or attention control app on the participant’s personal smartphone or on a smartphone provided by the study. The unmasked research assistant will provide written (and verbal, if requested) instructions on app use. They will provide as-needed technical assistance when requested in person or by phone and receive biweekly reminders to engage with their assigned app.

### Description of the Attention Control App

Participants randomized to the attention control group will receive the Dementia Guide Expert app, an existing BPSD mobile app freely available in the Google and Apple app stores. It was developed by the ENGAGE-IL initiative at the University of Illinois at Chicago (Health Resources and Services Administration grant U1QHP28730). Dementia Guide Expert provides education only, with no interactive BPSD management support, coaching, assessment, or external response. It contains “evidence-based expert information on what dementia is, types, contributing factors, risks, symptoms, stages, diagnosis, tests, treatment, management, communication techniques, and links to resources and support services” [47]. We will use an attention control comparator to mimic the intervention group’s use and access to technology, frequency and type of contact with research staff (ie, for installation and technical support), and expectancy of benefit [48].

### Inclusion and Exclusion Criteria

Eligibility will be assessed using a screening questionnaire (Textbox 2).

Inclusion and exclusion criteria.
**Inclusion criteria**
Self-identified primary care partners of patients diagnosed with Alzheimer disease and related dementias (ADRD; at any stage) who are receiving primary care and community dwellingParticipants are English literate
**Exclusion criteria**
Participants cannot speak EnglishThey are involved in another trial that would prevent or interfere with study objectives (eg, another trial with an intervention aimed at reducing caregiver burden)Participants have a sensory or other impairment prohibiting the use of a mobile touchscreen device or another study activity (after correction).The patient with ADRD is a permanent resident of an extended care facility (eg, a nursing home, hospice facility, or locked memory unit of an assisted living facility).

### Recruitment and Retention

We will obtain lists of eligible care partners’ contact information from partner health systems or work with the health system to contact potentially eligible individuals as approved by the Indiana University Institutional Review Board (IRB), health system IRB (when applicable), and health system leadership. We will also obtain contact information for potential participants via word of mouth.

Research staff will call eligible care partners to determine if they are interested in study participation. Screening for eligibility will be conducted by phone or in person, when necessary, using a scripted questionnaire assessing eligibility. Data collection will occur remotely over the phone or videoconferencing software to minimize the burden on study participants. Research staff will also maintain engagement through regular contact with participants.

### Ethical Considerations

This trial is approved by the Indiana University IRB (15749) and is registered on ClinicalTrials.gov (NCT05733520). Indiana University Health system has approved the study through their internal approval system (they do not have an independent IRB), and the Community Health Network IRB has approved the distribution of study recruitment materials in their clinics. All protocol modifications will be approved by the IRB before implementation.

Informed consent will be obtained from participants by a research staff member. Individuals will receive verbal and written information about consent and offered a chance to have all their questions answered. Each participant will provide verbal documented consent over the phone.

As there will be no researcher interaction with the patient with ADRD or direct data collection from them, patients with ADRD will not be considered study participants or consented into the study.

Participants may withdraw from or discontinue the study at any time, including following the death of the patient with dementia or their placement in an extended care facility, by contacting a member of the research team. Participants may also be withdrawn, with notification, from the study to protect data integrity or if there is a danger to their or the research team’s safety related to continued participation. The risks of participation in this trial are expected to be minimal. Research personnel will be IRB approved and will have completed human subjects training, regular education, and updates on HIPAA regulations. Data will be stored in REDCap (Research Electronic Data Capture; Vanderbilt University), which is a widely used and secure browser-based, metadata-driven electronic data capture software solution and workflow methodology for designing clinical and translational research databases. Participants will be given a unique study ID to protect confidentiality and will not be identified in reports. Data collected through the Brain CareNotes app will be housed on HIPAA-compliant, secure cloud-based servers. Direct access to the app requires the user to input their email or phone number to which a one-time log-in code will be sent. After their first log-in, participants will also have the option to use their smartphone’s built-in biometric authentication (eg, fingerprint or facial recognition) to access the app. The only changes to log-in protocols will be those that result in equal or better security.

### Randomization

We will use a permuted block randomization scheme implemented within REDCap. Randomization will be stratified by recruitment source. Participants will be randomized after the baseline assessment by unmasked research staff. Research personnel masked to the randomization of individual participants will perform all primary and secondary data collection at the 6- and 12-month follow-ups. Participants will not be informed which app is the intervention and which is the control.

### Assessments and Outcomes

A research staff member will perform a baseline assessment with the participant before randomization and follow-up assessments at 6 and 12 months, as shown in Table 2. The research staff completing primary and secondary data collection for the 6- and 12-month follow-up assessments will be masked to the treatment condition. The research staff completing usability and acceptance data will be unmasked to the treatment condition. All assessments will be scheduled and conducted remotely over the phone or with videoconferencing software (eg, Zoom; Zoom Communications, Inc) or in person when necessary. Participants will receive US $25 per assessment period with an additional US $25 bonus if they complete all 3 assessment periods (for up to US $100 for the entire study).

**Table 2 table2:** Assessment completion schedule.

	Baseline	Month 6	Month 12
Patient functional abilities (FAQ^a^)	✓		
Patient dementia stage (QDRS^b^)	✓		
Patient Care partner demographics	✓		
Neuropsychiatric Inventory	✓	✓	✓
Care partner depressive symptoms (PHQ-9^c^)	✓	✓	✓
Care partner acute care use		✓	✓
Patient acute care use		✓	✓
Care partner self-efficacy	✓	✓	✓
Care partner social support (MSPSS^d^)	✓	✓	✓
App usability (SUS^e^)		✓	✓
Behavioral Intention Questionnaire		✓	✓

^a^FAQ: Functional Activities Questionnaire.

^b^QDRS: Quick Dementia Rating System.

^c^PHQ-9: 9-item Patient Health Questionnaire.

^d^MSPSS: Multidimensional Scale of Perceived Social Support.

^e^SUS: System Usability Scale.

The primary outcomes assessed are (1) patients’ BPSD and (2) care partner burden. The secondary outcomes assessed are (1) care partner depressive symptoms and (2) patient and care partner acute care use.

Care partner burden and patients’ BPSD will be determined using the NPI [32,33], administered by research staff to the participant at baseline, 6 months, and 12 months. The NPI has been adopted by the Alzheimer’s Disease Cooperative Studies Group [49,50] to obtain information in 12 behavioral areas including delusions, apathy, hallucinations, disinhibition, agitation, depression, aberrant motor behavior, anxiety, nighttime behavior, and euphoria [32,33]. The NPI has both content and concurrent validity as well as between-rater, test-retest, and internal consistency reliability [32].

Care partner depressive symptoms will be assessed using the PHQ-9 [34,35], administered by research staff at baseline, 6 months, and 12 months. The PHQ-9 is a 9-item depression scale that has good internal consistency and test-retest reliability as well as convergent, construct, criterion, procedural, and factorial validity for the diagnosis of major depression [34,35,51-53].

We will also ask participants to self-report any acute care use in the preceding 6 months by themselves or the patient with ADRD during the 6- and 12-month follow-up visits.

### Additional Data Collection

To collect contextual information regarding the severity of the care recipient’s dementia, we will assess the care recipient’s functional abilities and dementia stage at baseline. The FAQ [42] and the QDRS [43] will be administered by research staff to the participant at baseline to assess the cognitive and functional status as well as the dementia severity of the patient with ADRD.

We will also collect patient and participant demographics at baseline, including age, sex, gender, race, ethnicity, education level, income, and living situation.

In addition to the primary and secondary outcomes, we will also measure (1) care partner self-efficacy, (2) care partner social support, (3) app acceptance, and (4) app usability throughout the study.

Care partner self-efficacy will be measured using the Revised Scale for Caregiving Self-Efficacy [36], and care partner social support will be measured by the MSPSS [37]. They will be administered by research staff to the participant at baseline, 6 months, and 12 months. Both scales have been validated in ADRD care partner samples, have strong psychometric qualities yet are brief, and measure constructs hypothesized and shown to act as the mechanisms of action for other psychosocial ADRD care partner interventions [30,31].

For both the control and intervention apps, we will assess app acceptance and app usability with surveys at the 6- and 12-month follow-ups. We will assess usability using the Simplified System Usability Scale [38], a 10-item questionnaire answered on a 5-point Likert scale (from strongly disagree to strongly agree). Technology acceptance will be assessed using the Behavioral Intention Questionnaire, a 4-item questionnaire using a 7-point response scale from 0 (not at all) to 6 (a great deal) [39,40].

### Analyses

At 12 months, the NPI Caregiver Distress scale will be compared between study groups using an analysis of covariance model with fixed effects for Brain CareNotes (vs attention control), health system, age, sex, race, recruitment source, and baseline values for NPI Caregiver Distress and NPI Total Score scales. For between-group comparisons, the difference in least squares means, corresponding SE, 2-sided 95% CIs, and 2-tailed *P* value will be derived from this analysis of covariance model and presented. Within-group change (least squares) means, corresponding SEs, 2-sided 95% CIs, and 2-tailed *P* values will also be presented. Standard model diagnostics will be performed to assess the validity of the proposed model; these diagnostics will include an examination of the residuals for normality, linearity, and homoscedasticity as well as testing for the significance of the intervention by baseline values interaction term to examine if intervention effect differs depending on the baseline levels of NPI Caregiver Distress or NPI Total Score scales.

The NPI Caregiver Distress scale will also be analyzed using a generalized linear mixed model (GLMM) [54,55] with an identity link function. GLMM allows us to analyze longitudinal data at each time point (baseline, 6 months, and 12 months) adjusting for multilevel dependencies within an individual (nested in the study group) and to explore additional covariates as mentioned earlier. Random intercepts, slopes, and fixed covariate effects will be estimated as needed. Time will be modeled as a continuous and categorical variable to model linear and nonlinear changes in care partner burden, respectively. The interaction between study group and time (ie, days between assessments) will be tested to determine if the rate of change in care partner burden is different between study groups. Standard model diagnostics will be performed to assess the validity of proposed models; these diagnostics will include examining the residuals for normality, linearity, and homoscedasticity and testing for the significance interaction term of the intervention by the baseline levels of the NPI Caregiver Distress and NPI Total Score scales. The variance-covariance structure of the random effects will be dependent on the variability among participants within groups. A preliminary test will be conducted to assess the significance of the homogeneity of variances [56] for within-group differences.

Analysis for patients’ BPSD and care partner depressive symptoms will be the same as for care partner burden, using the NPI Total Score scale and PHQ-9, respectively.

Acute care use will be analyzed as a dichotomous outcome (ie, yes or no for at least 1 emergency department or hospital visit—cumulative incidence) using a generalized linear model, specifically, a log-binomial regression model with fixed effects for Brain CareNotes (vs attention control), strata, and covariates described earlier. For the between–study group comparison, the estimated risk ratio (relative risk), SE, 95% Wald CI, and *P* value will be presented. Standard model diagnostics to assess final model validity and assumptions will be implemented.

As in the primary analysis, we will use a GLMM [54,55] with a log link function to model cumulative incidence. In addition, a Poisson model (GLMM with log link function and offset variable for follow-up duration) will be examined to model the incidence rate of acute care visit counts during the 12-month follow-up period.

The potential for 3-way and 2-way interactions will be examined to identify participant characteristics associated with increased benefit of the intervention. If statistically significant interactions are observed, additional intervention effect results will be presented as subgroup analyses to highlight intervention effect modifiers on primary and secondary outcomes separately.

Measures related to improved psychosocial outcomes (ie, social support and self-efficacy) will be tested as a potential mediator or moderators of intervention effects. We will also examine baseline characteristics (eg, sex and age) related to psychosocial outcomes as potential intervention effect moderators.

Similarly, mechanism measures (MSPSS and Revised Scale for Caregiving Self-Efficacy) will be evaluated for their potential mediation effect on the primary and secondary outcomes. We will also use investigate patient characteristics (FAQ or QDRS) as potential moderator. All analyses related to study primary, secondary, and mechanism outcomes will be performed by researchers masked to treatment condition.

Linear regression and classification and regression trees will be used to examine the effect of intervention timing, participant ratings on usability, acceptance, and actual use of technology on intervention efficacy.

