### Sample Size

The sample size was determined to achieve at least 80% power to detect group differences on both primary outcomes: care partner burden and BPSD. Adequate power required 64 participants per group (or N=128 in total) based on previous work [16]. Conservatively estimating 75% retention, a target total of 160 was set.

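### Subgroup effects are presented when an interaction is significant, over an open-ended set of 2-way and 3-way interactions, which invites false and overestimated effect modifiers

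*Protocol article*

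**What the plan says.** The rule is in the protocol article under Methods, Analyses, and has two steps.

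- Search: "The potential for 3-way and 2-way interactions will be examined to identify participant characteristics associated with increased benefit of the intervention".
- Presentation: "If statistically significant interactions are observed, additional intervention effect results will be presented as subgroup analyses to highlight intervention effect modifiers". The sentence goes on to apply this to the primary and the secondary outcomes separately.

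The same section names candidate modifiers in several places. For the NPI analyses it plans "testing for the significance of the intervention by baseline values interaction term" for baseline NPI Caregiver Distress and baseline NPI Total Score, as part of model diagnostics. It then names social support and self-efficacy as possible mediators or moderators, gives sex and age as examples of baseline moderators, and will "investigate patient characteristics (FAQ or QDRS) as potential moderator". Because sex and age are only examples, the list is open. The model covariates ("health system, age, sex, race, recruitment source, and baseline values for NPI Caregiver Distress and NPI Total Score scales") and the recorded demographics ("age, sex, gender, race, ethnicity, education level, income, and living situation") could all enter.

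The article gives no number of interaction tests and no significance level for them, and does not call the search exploratory. Under Sample Size, power is stated only for group differences on the two primary outcomes: "Adequate power required 64 participants per group".

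**The concern.** Choosing which subgroup effects to show by whether the interaction reached significance is a stated rule, not a detail left open. Applied to many candidates, it will produce some modifiers by chance. Applied in a trial sized for main effects, it will miss most real interactions of moderate size and overestimate those that it passes. The article describes the results as highlighting effect modifiers, so readers could take them as evidence about which care partners benefit from Brain CareNotes. The treatment comparisons on the primary and secondary outcomes are not affected.

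**Working it through.** The article gives no figure on this point, so there is nothing to reproduce. The following shows what the rule would yield.

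**Inputs**
- Level: two-sided 0.05. This is an assumption, in line with the main model, for which "2-sided 95% CIs, and 2-tailed *P* value will be derived from this analysis of covariance model".
- Candidates expressly named as interaction terms or moderators under Analyses, k = 8: baseline NPI distress, baseline NPI total, social support, self-efficacy, sex, age, FAQ, QDRS.
- Outcomes: NPI distress, NPI total, PHQ-9, patient acute care use, care partner acute care use. That is five if acute care use is counted separately for each person.
- Evaluable participants: 160 × 0.75 = 120, or 60 per arm (Sample Size).

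**False modifiers per outcome if there is no true modification**

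Expected number = 0.05 × m for m tests. This needs no independence. The chance of at least one, if tests are independent, is 1 − 0.95^m.

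| Reading of the rule, k = 8 | m | Expected per outcome | At least one | Expected over 5 outcomes |
|---|---|---|---|---|
| 2-way only | 8 | 0.4 | 1 − 0.95^8 = 34% | 2.0 |
| 2-way, plus group × time × characteristic | 8 + 8 = 16 | 0.8 | 1 − 0.95^16 = 56% | 4.0 |
| 2-way, plus treatment × every pair | 8 + 28 = 36 | 1.8 | 1 − 0.95^36 = 84% | 9.0 |

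Sensitivity to the unstated number of candidates:
- k = 5: 0.25 (2-way only) to 0.75 (15 tests, every pair).
- k = 7, the model covariates: 0.35 to 1.4 (28 tests).
- k = 16, every characteristic named, with demographics counted once: 0.8 to 6.8 (136 tests).

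A simulation of null data (120 participants, 1,000 runs, modifiers generated independently of each other) gave totals of 0.76 for k = 5 and 1.36 for k = 7, close to 0.75 and 1.4.

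**Power and overestimation**

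Take a continuous outcome in SD units and a balanced binary modifier (an assumption), with normal approximation and no gain from covariate adjustment.

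- Main effect: SE = √(2/60) = 0.183.
- 2-way interaction: SE = 2 × 0.183 = 0.365. Power for 0.5 SD = Φ(0.5/0.365 − 1.96) = 28%. With 64 per arm it is 29%.
- 3-way interaction: SE = 4 × 0.183 = 0.730. Power for 0.5 SD = Φ(0.5/0.730 − 1.96) = 10%.
- Smallest significant estimate: 1.96 × 0.365 = 0.72 SD (2-way) and 1.96 × 0.730 = 1.43 SD (3-way).

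A true 2-way interaction of 0.5 SD can therefore pass the trigger in the right direction only if its estimate is at least 0.72/0.5 = 1.4 times too large.

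**The case against.** Requiring an interaction test before subgroup effects are shown is a conventional safeguard against reading effects off separate subgroups. A closed list of modifiers, a multiplicity adjustment and an exploratory label are things that a condensed article may leave to an analysis plan, which is not shown here. Their absence is therefore not the finding. What stands is what the article itself fixes: the significance trigger and the 3-way search. A list elsewhere would remove neither.

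The count of eight can also be disputed. The baseline NPI interactions are planned as diagnostics. Social support, self-efficacy, FAQ and QDRS are named in separate sentences that carry no significance condition. This is a fair limit on any single figure, and is why a range is given. On the other side, the rule does promise 3-way terms and its examples are open-ended, so the 2-way-only line is the low end for a given k.

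The power figures assume a balanced binary modifier. Several candidates are scales or continuous. For a standardised continuous modifier the SE of the 2-way slope interaction is about √(4/120) = 0.183, and the threshold about 1.96 × 0.183 = 0.36 SD per modifier SD. Baseline adjustment would improve precision, and the figures do not apply to the binary acute care outcomes.

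A reader might infer four stronger points that the article does not support:
- That all interactions will be tested. It says only that their potential will be examined.
- That several false modifiers per outcome must be expected. That needs about 10 or more candidates with every pairwise 3-way term (55 tests, 2.75 expected at k = 10).
- That the reported modifiers would be mostly noise. That depends on how many true modifiers exist, which is unknown.
- That non-significant interactions will be withheld. The condition governs the additional subgroup results, and nothing is said about withholding the interaction tests.

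**Conclusion.** The concern holds as a badly fixed rule of moderate weight. Presentation of subgroup effects depends on significance, over an open-ended set of 2-way and 3-way interactions and for each primary and secondary outcome. For the eight named candidates, about 0.4 to 1.8 false modifiers per outcome are expected, with a 34% to 84% chance of at least one. These figures assume a two-sided level of 0.05 and no true modification, and the chances also assume independent tests. Broader candidate sets give more. For balanced binary modifiers and about 120 evaluable participants, real interactions of 0.5 SD would usually be missed (28% power for 2-way, 10% for 3-way), and those that pass would tend to be overestimated. No single count of false findings can be stated, because the article does not give the number of tests.

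**What to change.** Before analysis starts, replace the two-step rule under Analyses with the following:

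1. Examine only 2-way interactions of treatment with a short, named list of baseline characteristics already collected (for example baseline NPI score, QDRS stage and care partner sex).
2. Drop the 3-way search.
3. Report every examined interaction estimate with its 95% CI, whether or not it is significant. Do not make subgroup presentation depend on a P value.
4. Label these results hypothesis-generating.

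Multiplicity control within each outcome (Holm or false discovery rate) is optional, since formal adjustment of exploratory tests is debatable. If an analysis plan already holds a list, the article's rule should be aligned with it.

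The cost is a change of wording, with no change to data collection or sample size. The downside is that fewer exploratory subgroup statements can be made.
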